### Conceptual Framework: A Value-Based Approach

To compare the different care setting possibilities for ambulatory emergency patients, we propose value-based assessment, an approach first described by Michael Porter in 2006 [58,59] and widely adopted since by researchers and health quality organizations around the world [60-66]. Value is defined in terms of health outcomes achieved per dollar spent [58,67,68]. It promotes the best care at the lowest cost, without isolating clinical issues from economic issues. Two essential components are needed: (1) a feasible and reliable costing method and (2) valid, reliable, and readily available outcome indicators, consistent with the priorities of patients, deciders, and care providers. This comprehensive paradigm aligns patients, deciders, and clinicians behind shared goals, based on patient preferences and scientific evidence.

### Previous Preliminary Work

Our team has conducted a pilot study in which an ED and a primary care clinic offering walk-in services for frequent ambulatory acute conditions were compared in terms of costs of care and compliance with practice guidelines [69,70]. We reviewed the medical records of 918 adults with one of 13 targeted ambulatory acute conditions during the 2015 and 2016 fiscal year and applied a time-driven activity-based costing method. Time-driven activity-based costing has been found to provide more precise accounting than methods based on diagnosis-related groups and is simpler than conventional activity-based costing [41,71-73]. It assumes that the cost of a care episode is proportional to the time that the patient spends receiving the care. Costs of care are determined by allocating all direct costs (eg, staff salaries) and overhead (eg, building maintenance) to activities related to patient care, including physician charges [74,75]. This costing method has been used successfully in many care settings [65,71,76,77], and we adapted it for use in EDs and primary care practices [41,69,78,79]. The adjusted mean costs in each clinical setting for upper respiratory tract infection (URTI), a condition for which antibiotics and x-rays are generally not recommended [80,81] were determined and the clinical settings were compared on the basis of the process of care applied (Table 1).

**Table 1 table1:** Mean cost of care and percentage of use of nonrecommended care applied to upper respiratory tract infection in a primary care practice and an emergency department.

Variable		Primary care practice (n=102)	Emergency department (n=52)	*P* value
Cost of care^a^ (US $), (mean 95% CI)		45.4 (38.4-53.4)	59.8 (49.4-72.3)	<.001
**Process of care, % (95% CI)**				
	Chest x-ray	13.7 (7.7-22.0)	26.9 (15.6-41.0)	.05
	Antibiotics	44.1 (34.3-54.3)	5.8 (1.2-16.0)	<.001

^a^Mean value adjusted for age, sex, vital signs, comorbidities, and number of regular medications for upper respiratory tract infection.

On the basis of this preliminary study, we conclude that (1) time-driven activity-based costing is feasible in ED and primary care settings without requiring advanced information technologies or rigorously coded electronic medical records, 2 major barriers to conducting research in outpatient clinics, and (2) significant variations in costs and quality of care may exist between EDs and clinics, suggesting that a multicenter cohort study is warranted. However, this retrospective study highlighted major issues that only a prospective design can resolve: comorbidities (crucial to risk adjustment), disposition plans (crucial to assessing quality of care), and discharge diagnosis are not readily extractable from databases in the outpatient setting and are often missing or incomplete in medical notes. By manually reviewing thousands of visits logged in electronic records, our research assistants identified eligible cases one chart at a time. These major hurdles apply to outpatient clinics in all Canadian provinces. A retrospective design for a multicenter cross-jurisdictional study would have major methodological flaws because of the unlikeliness of obtaining comparable information across settings. More importantly, a retrospective study on administrative databases would not allow us to assess patients’ perspectives. Finally, a randomized controlled trial is not feasible for the population and settings under study because randomization would have to occur before any contact with the health system to assign patients to their treatment group. For these reasons, we believe that a prospective cohort study is the most appropriate design for identifying the best care setting for ambulatory emergency patients.

### Objectives

Our goal is to compare the health outcomes and costs of care received in EDs, walk-in clinics, and primary care practices by ambulatory patients presenting with acute respiratory conditions, namely, URTI, sinusitis, otitis media, pharyngitis, tonsillitis, bronchitis, influenza-like illness, pneumonia, acute asthma, or acute exacerbation of chronic obstructive pulmonary disease (COPD). We selected these conditions because many performance metrics have been validated previously for assessing the quality of care provided [82,83]. Highly prevalent in ambulatory emergency care before the COVID-19 pandemic [16,50], acute respiratory conditions are now putting even greater strain on already overstretched health care systems. In addition, the pandemic has shifted primary care services significantly toward telemedicine (ie, remote consultation by phone or videoconferencing) [84]. Determining where these patients can get the most effective care is a crucial issue. Our 3 specific objectives are to (1) estimate the costs of care processes administered by care providers in EDs, walk-in clinics, and primary care practices for acute respiratory conditions from the public payer’s perspective; (2) estimate and compare the cost of care episodes in EDs, walk-in clinics, and primary care practices for acute respiratory conditions from the public payer’s and patient’s perspectives; and (3) compare patient health outcomes and quality of care in these care settings when treating acute ambulatory respiratory conditions from the public payer’s and patient’s perspectives. To achieve these objectives, we propose a 4-year (from April 1, 2021, to March 31, 2025) research plan in 2 phases: a time-driven activity-based costing method study (objective 1) and a prospective cohort study (objectives 2 and 3).

## Methods

### Phase 1: A Time-Driven Activity-Based Costing Method Study

#### Setting

A time-driven activity-based costing study will first be performed for fiscal year April 1, 2021, to March 31, 2022. We shall estimate the cost of care processes administered by care providers (Objective 1) in 3 different models of ambulatory emergency care in Québec and Ontario: (1) discontinuous care in the ED (by physicians unfamiliar with the patients); (2) discontinuous care in a walk-in clinic (by physicians unfamiliar with the patients); and (3) continuous care in primary care clinic (patients attached to a primary care practice, seen by their family physician or a colleague on a same-day appointment for urgent needs).

We have confirmed the participation of 14 of the 15 planned patient recruitment sites (ED 5/5, walk-in 5/5, primary care 4/5; Multimedia Appendix 1). They have been selected in different types of urban areas, including small (Joliette), medium (Kingston), large (Québec City, Ottawa), and metropolitan (Montreal) cities. In each participating region, an ED will be paired with a nearby walk-in clinic and primary care practice. We are currently securing our final additional clinic in Ottawa with the help of BeACCoN (Better Access and Care for Complex Needs), a provincial primary care research network.

#### Design

The time-driven activity-based costing method [72,85] will enable us to derive for each setting the cost of care processes (eg, triage) and traceable supplies (eg, medication) potentially provided to patients with acute respiratory conditions, which includes telemedicine. This costing method requires only 2 parameters, namely, the unit cost of supplying capacity and the duration of processes, and comprises the following steps:

Process (eg, salbutamol in acute asthma) and resource (eg, respiratory therapist) mapping through discussion with local teams for each respiratory condition (Figure 1)Validation of process maps and durations by on-field research assistants prospectively observing patients and measuring process duration using time-motion software (UMT Plus [Laubrass])Calculation, with local administrative teams, of total annual overhead costs (eg, building maintenance) related to the care of ambulatory patients with acute conditions (Multimedia Appendix 2 for allocation rules)Estimation of cost per time unit ($/minute) for the following cost elements obtained by dividing yearly expenses for a cost element by the total yearly number of minutes worked by professionals to care for patients in this facility (Multimedia Appendix 3): (1) human resources (eg, nurses, physicians) or equipment (eg, x-ray machine), (2) consumable supplies (eg, gloves, needles, paper), and (3) overhead costsEstimation of the cost of traceable supplies (eg, laboratory testing)Calculation of the average cost of each health care process (Multimedia Appendicies 3 and 4)

**Figure 1 figure1:**

Process mapping for upper respiratory tract infections in the emergency department (truncated). Each box represents a process with its duration. Colors identify human resources (red=nurses; yellow=clerks; green=physicians). ED: emergency department.

The cost of a care process is proportional to the mean duration measured on field. For example, the cost of triage is estimated by adding up the expenses associated with the triage nurse, consumables, and overhead. These elements will be estimated by multiplying the mean triage duration by their unit costs as follows:

Cost of triage = mean triage duration × (unit cost of nurse + unit cost of consumables+ unit cost of overhead) = 7.1 min × (US $0.78/min + US $0.07/min + US $0.17/min) = US $7.24 (Can $1 [US $0.76])

The cost of telemedicine will be estimated following the same steps, from resource mapping and time measurement through allocation of overhead and consumables, all the way to average cost calculation.

Where applicable, the following adjustments will be made so that the estimated costs reflect the public payer’s perspective: (1) expenses paid by physicians or owners of a participating clinic will be subtracted from the yearly expenses related to the appropriate cost element (eg, salaries, overhead); (2) similarly, government funding received by a clinic apart from physician remuneration will be added.

#### Financial Data Sources

The accounting department at each participating site will provide all financial data, except for physician charges. To calculate the unit cost for physicians, the total amount charged by all physicians per site per year will be obtained from local private billing agencies. This sum will be divided by the number of minutes spent delivering patient care, which will be obtained from physician schedules.

#### Intermediate Outputs of Phase 1

In addition to institution-specific costs, upon completing phase 1, we will create a list of standardized costs of care for each process and associated traceable supplies based on the average costs estimated in the 15 institutions (ED, walk-in, primary care, both provinces). Use of standardized costs will eliminate price effects because of differential costings between sites and provinces, thereby facilitating comparisons between the 3 clinical settings. In phase 2, the cost of a care episode will be calculated per individual by summing the standardized costs of care processes, supplies, and drugs received by each patient during their visit. Fixed and variable costs will be broken down to estimate and compare the care settings in terms of the marginal cost of each new patient assessed [86].

### Phase 2: A Prospective Cohort for Comparing the 3 Health Care Settings

#### Design and Setting

A multicenter prospective cohort study will be conducted in the institutions included in phase 1 to compare the value of care in EDs, walk-in clinics, and primary care practices (Objectives 2 and 3).

#### Selection of Participants

We shall include patients (1) aged 18 years and older; (2) seen in person or via telemedicine in an ED, a walk-in clinic, or the primary care practice where they are registered; (3) ambulatory during the entire visit or consultation; and (4) discharged home with a diagnosis of URTI, sinusitis, otitis media, pharyngitis, tonsillitis, bronchitis, influenza-like illness, pneumonia, acute asthma, or acute exacerbation of COPD. We shall exclude patients (1) transported by ambulance, (2) not covered by the provincial health insurance plan, (3) having consulted for a similar problem in the previous 30 days as patients with refractory diseases representing a population with different care needs, (4) living in a long-term health care facility or incarcerated, or (5) receiving palliative care.

#### Recruitment Procedures on the Initial Visit

A research nurse in collaboration with local clerks at each site will screen eligible patients after on-site registration or web-based scheduling, but before assessment by a physician, based on presenting complaints suggestive of acute respiratory conditions. After assessment and once a targeted diagnosis is confirmed, the same research nurse will prospectively (1) obtain consent from patients; (2) ensure that the discharge diagnosis, comorbidities, and disposition plans are fully documented; and (3) administer a questionnaire to assess patient experience of care and motivation for choosing one care setting over the other. Motivation will be classified into the 6 domains of the Conceptual Model of Emergency Department Use [35]. Participants will be asked to specify whether their choice of care setting was based on accessibility, convenience, their perception of the severity of illness, their beliefs and knowledge regarding these care settings, referral and advice from a care professional or an acquaintance, or costs. They will also be requested to rate their perception of illness severity. For on-site participants only, the research nurse will also (1) assess the severity using the Pandemic Medical Early Warning Score (PMEWS), a validated severity score allowing points for age, vital signs, comorbidity, social situation, and functional status [87], and (2) perform spirometry (measured parameter: forced expiratory volume in the first second [FEV_1_]) on patients with acute asthma. A random sampling recruitment schedule will be planned to ensure a proportional representation of the hours of operation for each recruiting site. Participating EDs will recruit on a schedule similar to their paired participating clinics to include participants who could have consulted in an alternative setting and exclude night patients who differ significantly from patients seeking care during the day [88]. Recruitment will occur over a full year to encompass seasonal variability in the incidence of respiratory diseases.

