**Secondary**			
	Median PROM-ED^d^ patients scores (O)	Developed and validated by team member SV, the PROM-ED questionnaire provides a measurement of patient-reported outcome expressed as scores for symptom relief, understanding of health concern, reassurance, and having a plan for care [91,94].	Follow-up call at 10 days
	Median scores on a PREM^e^ (O)	We adapted and are validating a tool from patient experience surveys used in EDs and primary care clinics in Ontario [100-102]. This tool evaluates the patient’s view of care delivery and measures various dimensions of patient experience relevant to all care alternatives, such as attitude of providers.	At the end of the initial visit
	Mean CoPaQ^f^ (C)	A questionnaire measuring patients’ and caregivers’ out-of-pocket expenses (eg, travel) and indirect costs (eg, loss of income) will be proposed to participants. This questionnaire was developed and validated by members of our team (ML, JG, SB) and further adapted for use in this study.	Follow-up call at 10 days
	Incidence of admission, intensive care unit, or mortality (O)	Proportion of patients who were admitted to the hospital or the intensive care unit or died because of one of the targeted respiratory conditions within 30 days [83,103] after the initial visit.	Provincial databases: Med-Echo, ICES, death registries
	Wait times	Median and mean length of stay and time spent waiting to see a physician.	Electronic medical records

^a^O: health outcome.

^b^ED: emergency department.

^c^C: health cost.

^d^PROM-ED: patient-reported outcome measure for ED.

^e^PREM: patient-reported experience measure.

^f^CoPaQ: cost-for-patient questionnaire.

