#### Statistical Analysis

All main analyses will be conducted primarily on participants assessed in person in any of the care settings. Participants assessed by telemedicine will be analyzed and compared separately between sites where it is implemented. The value delivered at each participating site and on average in each care setting type will be illustrated with an operational effectiveness graphic [114]. Adjusted costs of care for acute ambulatory respiratory conditions will be plotted on the x-axis and adjusted return visits within 72 hours on the y-axis. Points closest to 0 on both axes represent the highest value of care (Multimedia Appendix 6). Indeed, the lower the return visit proportion and cost of care, the higher the value of care. Similar graphics will be used for patient-centered outcome measures. To compare EDs, walk-in clinics, and primary care physician practices, multilevel generalized linear models will be used with probability distributions adapted to the outcome under evaluation. To adjust for confounding (differences in case mix between care settings), an overlap weights approach [115,116] will be used, wherein each individual receives a weight factor that is proportional to the inverse of the probability of choosing a particular setting. Subjects that differ fundamentally between settings are attributed a weight of 0 and are thus excluded. This approach is of the greatest interest when groups are initially very different [116]. Intuitively, overlap weights create a pseudopopulation for which treatment is independent of measured confounders, thus mimicking a randomized trial of those confounders. Overlap weights have been shown to be more robust than conventional inverse probability weighting and matching based on propensity scores [115]. The weights will be estimated using a multinomial logistic regression model in which the dependent variable is the chosen care setting and independent variables are potential confounders or risk factors [117] for the outcomes identified in the literature: age [118,119], sex and gender [118,120], ethnicity [118,121-123], registration with a family physician [20,124], comorbidities (the Charlson index; number of regular medications) [118,125,126], asthma, FEV_1_ among patients with asthma, the Canadian deprivation index [127-129], patient perception of illness severity [130], and vital signs [131-135] as proxies for severity. The same independent variables will be used to adjust for differences in case mix between settings in the telemedicine cohort, excluding vital signs and FEV_1_. Multiple imputation will be considered as a possible means to adjust for these variables in this cohort. Overlap weights will be calculated using the values predicted by this model. We shall verify that the care setting groups are comparable according to the measured confounders after weighting by computing standardized mean differences. Differences below 10% will be considered to indicate good balance [117]. If residual imbalances are present, the weighting model will be revised. Once an appropriate balance is achieved, separate models for each outcome will be fitted to the weighted data, for which the care setting will be the only independent variable. The robustness of results with respect to unmeasured confounding will be assessed using the E-value [136,137]. Clustering by setting (eg, province, practice unit) will be taken into account using multilevel modeling (random intercept on province and practice unit). Reported cost estimates will be calculated with item-specific standardized costs (eg, Québec and Ontario average nurse unit cost). Patients referred to the ED from a participating outpatient facility but discharged home after ED assessment will be analyzed in the care setting group where they first presented, and the ED referral will be considered as a return visit. The costs of any return visits and admissions up to 7 days after the initial visit will be estimated separately and attributed to the care setting where the initial visit took place. Results of the 3 questionnaires from the patient perspective will be reported as proportions (PREM), mean costs (CoPaQ), and median scores (PROM-ED) and adjusted using the overlap weights approach. As patients seek care for symptoms, subanalysis based on presenting complaints instead of discharge diagnosis will be conducted to provide meaningful patient-oriented results. Other subanalyses will evaluate which patient profile (eg, gender [120], motivation for choosing a facility), and institutional characteristics (eg, access to x-ray) predict high quality and low costs, keeping in mind that our value assessment might not yield similar results for all subgroups or even within a group of patients with the same diagnosis. Statistical differences will be assessed with a significance threshold set at .05.

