
#### Sensitivity Analyses

To assess potential uncontrolled confounding of the results, sensitivity analyses will be conducted by excluding separately and concurrently the participants most likely to influence the effects of the 3 types of care settings: (1) ≥65 years; (2) with ≥1 comorbidity; (3) with either asthma or COPD; (4) with ≥1 regular medication; (5) with any abnormal vital signs; (6) in the lowest and highest quartile of the deprivation index; and (7) smokers. The analyses will be repeated using PMEWS instead of vital signs as a marker of illness severity. To control for a potential Hawthorne effect, the analyses will be repeated, with the first 3 months of recruitment excluded to focus on the data collected after the providers have become used to being observed.

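### Perceived severity and FEV1 enter the weighting model as baseline confounders but are collected after the physician's assessment, so the weights may adjust for effects of the care being compared

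*Protocol article*

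**What the plan says.** All references are to the protocol article, Methods, Phase 2.

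- **Before the physician.** Under Recruitment Procedures on the Initial Visit, the only nurse activity placed before the physician is screening: "but before assessment by a physician, based on presenting complaints suggestive of acute respiratory conditions".
- **After the physician.** The same section continues: "After assessment and once a targeted diagnosis is confirmed, the same research nurse will prospectively (1) obtain consent from patients". The nurse then gives the questionnaire on experience of care and motivation for choosing the setting. Of the participants it adds: "They will also be requested to rate their perception of illness severity".
- **On-site participants only.** The nurse also scores PMEWS and is to "perform spirometry (measured parameter: forced expiratory volume in the first second [FEV_1_]) on patients with acute asthma". No timing relative to treatment is given for either.
- **Arrival data.** Data Collection and Follow-Up Phone Calls specifies vital signs as those on arrival. It is the only severity measure with such an anchor.
- **Use in the analysis.** Statistical Analysis puts FEV1 (patients with asthma) in the propensity model, together with "patient perception of illness severity [130], and vital signs [131-135] as proxies for severity". For telemedicine, vital signs and FEV1 are dropped and perceived severity stays.
- **Sensitivity Analyses.** "The analyses will be repeated using PMEWS instead of vital signs as a marker of illness severity". Another analysis excludes patients with asthma or COPD.
- **What is compared.** Outcome Measures defines the unit of analysis as the initial visit, from arrival to discharge.

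**The concern.** Propensity weighting is meant to make the settings comparable on what patients brought with them. A covariate measured after care has begun can carry part of what the setting did. If one setting lowers the measured severity more than another, through information, reassurance or treatment, its patients look milder than they arrived. They are then balanced against patients elsewhere who really were milder on arrival, and that setting looks worse than it is.

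This matters because the Discussion (Challenges and Mitigation Strategies) relies on the overlap weights to overcome self-selection of the care setting. Perceived severity is collected from every participant, in person or by telemedicine. In the telemedicine analysis it carries more of the load, because vital signs and FEV1 are not available there.

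**Working it through.** **1. Order of events for each severity covariate**

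| Covariate | When collected, as written | Reference time stated? | Role |
|---|---|---|---|
| Vital signs | On arrival | Yes | Weighting model (in person) |
| Perceived severity | After assessment, diagnosis and consent | No | Weighting model (in person and telemedicine) |
| FEV1 (acute asthma, on site) | Same sequence | No | Weighting model (in person) |
| PMEWS (on site) | Same sequence | No | Replaces vital signs in one sensitivity analysis |

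The exposure runs from arrival to discharge, so rows two to four fall inside it as written. Most of PMEWS cannot move: age, comorbidity and social situation do not change during a visit. Only its vital signs, and possibly functional status, can.

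**2. Would the planned checks reveal it?**

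- *Standardized mean differences* are computed on the values entered in the model, so they can be near zero while arrival severity is unbalanced.
- *The E-value* addresses unmeasured confounding, not a measured covariate that care has altered.
- *PMEWS for vital signs* leaves perceived severity and FEV1 in the model.
- *Excluding asthma and COPD* removes the FEV1 problem in that analysis, but not perceived severity.
- No stated analysis uses arrival-time covariates only.

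**3. Why balance on the measured value can mislead**

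Let S be arrival severity in SD units, A = 1 for the setting that lowers the measurement by d, and e random error. The measured value is M = S − d·A + e. If weighting makes the mean of M equal in both groups, then

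weighted difference in S = d − weighted difference in e.

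Without measurement error this is exactly d. It is an identity, not an estimate: d has to be assumed.

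**4. Illustrative size**

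The documents give no before/after shift, so every input here is an assumption: two settings; log-odds 0.5 per SD of severity for choosing setting A and 0.6 per SD for a return visit; return-visit risk about 6 to 7%; error SD 0.5; true setting effect zero; overlap weights 1 − p for A and p for the other, with p the fitted probability of A; at least 2 million subjects per run. Ranges span two sets of runs.

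| Covariate used for weighting | False difference in return visits (percentage points) |
|---|---|
| None (unadjusted) | 1.7 to 1.8 |
| Severity measured on arrival | 0.3 to 0.4 |
| Measured after care, d = 0.25 | 1.0 to 1.1 |
| Measured after care, d = 0.5 | 1.8 to 1.9 |
| Measured after care, d = 0.75 | 2.6 |

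At d = 0.5 the weighted difference in M was 0.00 and in S 0.49 SD. The plan's balance limit is 10% (0.10).

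**5. Adding an arrival proxy, as the in-person model does through vital signs (d = 0.5)**

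| Error SD of the proxy | False difference (points) |
|---|---|
| 0.5 | 1.1 |
| 1 | 1.6 |
| 2 | 1.8 |

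The proxy reduces the bias by an amount that depends on how well it tracks severity. For scale, Sample Size targets a 5-point difference. In these runs setting A attracts the sicker patients and also lowers the measurement, so both errors point the same way. Other combinations could partly cancel.

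**The case against.** A reader might infer that the primary adjustment is shown to be biased. The documents do not go that far. They place the measurements after assessment, not after treatment. Salbutamol in asthma appears in Phase 1 as an example of a process to be mapped, and nothing says it precedes spirometry.

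The severity rating stands directly after the questions on why the setting was chosen, one of which concerns perceived severity. It may be meant as severity at the time of choosing, because late collection does not imply a late reference time. The questionnaire is not shown, and an article may leave item wording to the full protocol. This objection largely stands. It turns the point into *may condition* and makes the size unknown. It does not remove the point, because the article fixes both the collection sequence and the covariate list without tying the two together.

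A reader might also conclude that FEV1 should leave the primary model. That is a trade-off, since FEV1 is the only asthma-specific severity measure there. In the same simulation, with a weak arrival proxy (error SD 2) and d = 0.25, dropping the post-assessment measure left about 1.4 to 1.5 points of bias, against 1.1 when it was kept. With a good proxy or a larger shift, dropping it did better.

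A third inference is that adjusting for perceived severity adjusts away part of a secondary outcome, since PROM-ED is a "patient-reported outcome expressed as scores for symptom relief, understanding of health concern, reassurance, and having a plan for care". PROM-ED is collected at the 10-day call, and the documents do not show how far a visit-day rating overlaps with it. That remains a possibility only.

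**Conclusion.** The point holds in a limited form. As written, perceived severity (all participants) and FEV1 (on-site acute asthma) are collected inside the exposure window, without an arrival or pre-treatment reference, and are used as baseline confounders. The weights may therefore condition on effects of the care compared, and the planned diagnostics would not show it.

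The size cannot be derived from the documents. The 1.0 to 2.6 points are illustrations resting on assumed care effects of 0.25 to 0.75 SD and a single weighting covariate. Arrival vital signs, comorbidities and medications are unaffected by this and temper it in person. FEV1 concerns asthma only and is covered by the planned exclusion of asthma and COPD; perceived severity is not covered by any planned analysis. PMEWS is a minor matter, confined to one sensitivity analysis and to the components that can change during a visit.

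It should be settled before recruitment, because a missing reference time cannot be recovered at analysis.

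**What to change.** 1. Word the severity item so that it refers to when the patient decided to seek care. If the questionnaire already does so, say so in the protocol.
2. Score PMEWS from the arrival vital signs already collected.
3. Record the time of spirometry relative to any treatment given at the visit.
4. Add a weighting analysis restricted to arrival-time covariates, either without FEV1 or with only those FEV1 readings recorded as taken before treatment. Report it beside the primary model, which can keep FEV1.

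The cost is a severity item that relies on short recall, one time stamp and one extra analysis. Sample size and visit schedule do not change.
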